#### 3.9.2 Secondary outcomes

**Socioeconomic status:** a specialized questionnaire will categorize each family's socioeconomic level into one of five strata, providing a nuanced understanding of the economic conditions influencing participants' lives.**Health status:** participants' overall health will be assessed using four distinct questionnaires, covering a broad spectrum of indicators including physical functionality, pain levels, general health perception, vitality, social and emotional roles, and mental health. This comprehensive approach aims to capture the multifaceted aspects of health influenced by the intervention.

### 3.10 Statistical analysis

All statistical analyses will be performed using Stata 18.0 (44). Descriptive statistics will be calculated for both qualitative (e.g., categorical) and quantitative (e.g., continuous) data. Categorical variables, such as employment status or food security, will be summarized using frequencies and percentages, while continuous variables, such as household income or nutritional status (e.g., BMI), will be described using means and standard deviations for normally distributed data, or medians and interquartile ranges for non-normally distributed data.

For hypothesis testing, categorical variables like food security (measured as secure/insecure) and employment status (e.g., employed/unemployed) will be compared between the intervention and control groups using Chi-square tests or Fisher's exact tests, depending on sample sizes. For continuous variables, such as changes in household income or nutritional status (e.g., BMI, dietary diversity scores), Student's *t*-tests will be used if the data are normally distributed. If normality assumptions are violated, Mann-Whitney U tests will be applied instead.

To evaluate changes over time within the same group (e.g., baseline to 6 months), paired *t*-tests will be used for normally distributed continuous variables, such as income or BMI, while Wilcoxon signed-rank tests will be used for non-normally distributed variables. For categorical variables like food security status over time, McNemar's test will be applied.

Regarding regression models, linear regression will be used to assess continuous outcomes such as household income levels, nutritional status (BMI), or dietary diversity scores. Logistic regression will be applied to binary outcomes, such as food security (secure/insecure) or whether participants report improved health (yes/no). For outcomes with multiple categories, such as levels of health perception (good, fair, poor) or employment status (employed, unemployed, seeking work), multinomial logistic regression will be used.

To account for repeated measures over time (e.g., baseline, 6 months, and 12 months post-intervention), mixed-effects models (both linear and logistic) will be employed. These models will allow us to assess the effect of the intervention across different time points while controlling for intra-individual correlations. All hypothesis tests will be two-tailed, and a *p* < 0.05 will be considered statistically significant.

To align with the nature of the data, nutritional and health status variables will be analyzed at the individual level, allowing us to capture specific health outcomes for each family member. Socioeconomic variables, including food security (measured by the Household Food Insecurity Access Scale [HFIAS]) and dietary diversity, will be evaluated at the family level. This approach enables a comprehensive analysis by distinguishing between individual health measures and collective socioeconomic conditions.

For older adult participants, the *Mini Nutritional Assessment (MNA)* will be used to assess undernutrition risk. For all other participants, individual nutritional status will be determined through anthropometric measurements (weight, height, and age). Household-level dietary diversity will be measured with a dietary diversity questionnaire, enabling us to capture a broader picture of household nutritional intake.

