### 3.2 Participants and recruitment

The focus of this study is on the residents of a specific commune within the Colonche Parish, located in the Santa Elena province of Ecuador. The participant pool consists of families with an average monthly income of $463.93, a figure significantly lower than the cost of the Ecuadorian basic necessities basket, estimated at $789.57 (36, 37). The predominant educational attainment among community members is up to the primary level, facilitated by the region's publicly funded educational system. Each commune is home to ~3,875 individuals, distributed across 968 households. In addressing the needs of this community, the study aims to provide direct access to food for all participating families, leveraging the coastal commune's resources to enhance their food security and nutritional wellbeing.

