#### 3.5.3 Health situation

Health status was assessed using four questionnaires. These questionnaires were *the Short Form*-*36* Health Survey (*SF*-*36*) (40), *the Household Food Insecurity Access Scale* (*HFIAS*), *The World Health Organization Quality of Life* (*WHOQOL-100*) for adults (41), and *the Pediatric Quality of Life Inventory* (*PedsQL*) for children (42). These will include thirty-six, nine, hundred, and twenty-three questions, respectively.

To guarantee precision and contextual relevance for the Ecuadorian setting, we will employ Spanish-validated versions of all assessment tools.

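### Section 3.10 names only secure/insecure analyses for food security, although a nine-item scale is collected; the scale score should lead and the two-level result support it

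*Protocol article*

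**What the plan says.** Section 3.5.3 of the protocol article lists the HFIAS second of four questionnaires and gives their lengths as "thirty-six, nine, hundred, and twenty-three questions, respectively", so the HFIAS has nine items. The closing part of section 3.10 makes it the family-level measure: "food security (measured by the Household Food Insecurity Access Scale [HFIAS"]).

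Section 3.10 then treats food security as a category at each step where it appears:

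- Description: "Categorical variables, such as employment status or food security, will be summarized using frequencies and percentages".
- Between groups: "food security (measured as secure/insecure") is compared by chi-square or Fisher's exact test.
- Within group over time: "For categorical variables like food security status over time, McNemar's test will be applied".
- Regression: "Logistic regression will be applied to binary outcomes, such as food security (secure/insecure").

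The outcomes named as continuous are household income, BMI and dietary diversity scores. Those named as having several categories are health perception and employment status. Neither list contains an HFIAS score or a graded level of food insecurity. The article states no cut-off for secure, no reason for the split and no expected share of secure households.

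**The concern.** A two-level outcome registers change only when a household crosses the cut-off. A household that moves from severe to mild insecurity is concordant in McNemar's test. In the chi-square test and the logistic model it counts exactly like a household that has not moved. If the food forest reduces severity without bringing many households fully into security, the named analyses could show little or nothing.

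That pattern is realistic early on. Planting alone takes about nine months (section 4.2.1), and the repeated-measures example in section 3.10 ends at 12 months. The nine items will have been collected anyway, so the split saves no effort in the field. Section 3.10 also already plans linear mixed-effects models that could take the score.

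**Working it through.** **The plan's own figure.** Section 3.4 gives the only sample size calculation, which concerns the precision of a proportion:

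- n0 = 1.96² × 0.5 × 0.5 / 0.05² = 384.1; the article gives about 384.
- With the finite population correction for 968 families, 384.1 / (1 + 383.1/968) = 275.2, rounded up to 276, as stated.
- The 300 families per commune then follow from about 8% attrition, since 276/0.92 = 300.

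These figures reproduce, but none is a power, effect size or information figure for food security. The size of the loss therefore has to come from assumptions.

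**Inputs for the loss.** From the documents: nine HFIAS items (3.5.3), a two-level analysis (3.10), 300 families per commune (3.4), and two-sided tests at 0.05 (3.10). Assumed, because the documents are silent: a roughly normal underlying score and a share p of households classed as secure.

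**Formula.** The efficiency of a normal score cut into two levels, relative to the full score, is φ(z)² / [p(1 − p)], where z = Φ⁻¹(p). The loss is 1 minus this.

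| Share secure | φ(z)² / [p(1 − p)] | Relative efficiency | Loss | Equivalent of 300 households |
|---|---|---|---|---|
| 50% | 0.1592 / 0.25 | 0.637 | 36% | 191 |
| 30% | 0.1209 / 0.21 | 0.576 | 42% | 173 |
| 20% | 0.0784 / 0.16 | 0.490 | 51% | 147 |
| 10% | 0.0308 / 0.09 | 0.342 | 66% | 103 |

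The formula is symmetric, so 80% secure gives the same loss as 20% secure, and 90% the same as 10%.

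**Cross-check with a finite shift.** Take a shift of 0.2 SD towards secure (assumed), two equal arms of independent households, and 80% power. The score needs 393 per arm. The two-level version needs 620 at 50% secure, 758 at 20% and 1,049 at 10%. The ratios 393/620 = 0.63, 393/758 = 0.52 and 393/1,049 = 0.37 are close to the table. Only the ratios carry meaning, because the calculation ignores clustering by commune.

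**Sensitivity to the shape of the score.** A skewed score was simulated with nine items each scored 0 to 3 (total 0 to 27), secure defined as a total of zero, and assumed item thresholds and loadings. The loss was about 20% at 40% secure, 39% at 24%, 53% at 17%, 68% at 8% and 81% at 3%. There was a loss in every scenario, but its size depends heavily on the distribution and the cut-off.

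**The case against.** The strongest reply is that section 3.10 gives examples, not an exclusive list. It introduces its variables with phrases such as and like, and no sentence rules out analysing the HFIAS score. The article is condensed, and an analysis plan may hold the scoring detail. This stands in part: the score is not named, which is weaker than saying it will not be used. But the two-level form is stated outright and repeated for several tests, so it is a stated choice and not merely missing detail.

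Second, food security is not the primary outcome. Section 3.9.1 gives that place to nutritional status, and dietary diversity is kept as a score, so the household food domain retains one graded measure. This stands and limits the weight of the point.

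Third, secure/insecure status is easy to read and useful for policy, while a linear model on a bounded and perhaps skewed score has assumptions of its own. This also stands. It is a reason to keep the two-level result and to plan for skewness, but not to rely on that result alone.

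A reader might also infer from section 3.2 that most households must be insecure, since it describes "families with an average monthly income of $463.93" against a basket of $789.57, a ratio of 463.93/789.57 = 59%. The document does not support that step. The basket covers basic necessities in general, a mean does not describe a distribution, and the HFIAS measures access to food. A lopsided split is plausible but not shown.

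**Conclusion.** The point holds in a limited, conditional form. Every food-security analysis that section 3.10 names is categorical, so improvement short of the cut-off goes unseen and information in the nine items is lost. For a roughly normal score the loss is about 36% with half the households secure, 51% with 20% secure and 66% with 10% secure. Both the normality and the shares are assumptions.

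Two stronger readings should be avoided. A reader might take 36% to 66% as a property of this protocol. It is not: the range requires a roughly normal score and 10% to 50% secure (or 50% to 90% by symmetry), and the skewed simulation runs from about 20% to about 81%. A reader might also translate the loss into a drop in this trial's power. With one treated commune and one or two control communes (sections 3.1 and 3.3 differ on the number), variation between communes governs inference, and household-level power is not meaningful in absolute terms. The relative loss is the usable result.

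The change is worth making because it is nearly free, but it concerns an outcome that is not primary.

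**What to change.** In section 3.10, name the HFIAS score as the main food-security analysis. Use the mixed-effects model already planned, adjust for baseline score, and report the difference between groups with its 95% confidence interval. State in advance that if the score is strongly skewed or has many zeros, an ordinal model on the score or on graded levels will be used instead. Keep secure/insecure as a supportive result and state the cut-off that defines it.

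The cost is wording only, since the items are already collected. There are two downsides. A mean score difference is less immediate to read than a percentage, which the retained two-level result covers. A linear model on a bounded score also needs a check of its assumptions, which the ordinal alternative provides for.

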## 3 Methods

### 3.1 Study design

This study employs a randomized community trial design to assess the impact of a novel Food Forest reforestation technique that emphasizes the use of endemic and food-producing species. The goal is to enhance food sovereignty among coastal families in the Santa Elena Province, Ecuador. This initiative, a collaborative effort by Nedetel and CECAPROF Corporación Ecuatoriana De Capacitación (two companies that serve the area), aims to address the dual challenges of malnutrition and low average family incomes in the region (33). Participants for the study will be recruited from rural areas within the Colonche Parish of the Santa Elena Canton, a geographical area detailed in Figure 1 (34, 35). The study randomly allocated one commune to receive the Food Forest intervention, while a similarly characterized commune was randomly assigned as a control group, receiving no intervention. This randomization process ensures that the study meets the criteria of a randomized community trial. In consideration of ethical concerns, we have planned a delayed intervention for the control group. After the study period, the control commune will also receive the food forest intervention, contingent on securing additional funding. This phased approach allows for a scientifically rigorous assessment of the intervention's effects while ensuring that both communities ultimately benefit from the food forest initiative. The intervention strategy was developed based on insights from prior research, supplemented by consultations and interviews with experts in nutrition and reforestation, ensuring that the Food Forest initiative is ecologically viable and tailored to meet the nutritional and economic needs of the local communities involved.

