### 3.3 Sampling

In our study within Colonche Parish, we will engage in a randomized selection process to choose one commune for the treatment group, where the Nutritional Forest will be implemented, and two communes for the control group, which will not have access to the Nutritional Forest. This selection process will encompass all communes of the Parish, including Aguadita, Ayangue, Bajadita de Colonche, Bambil Collao, Bambil Desecho, Calicanto, Cerezal Bellavista, Febres Cordero, Jambelí, Las Balsas, Loma Alta, Manantial de Guangala, Manantial de Colonche, Monteverde, Palmar, Río Seco, Salanguillo, and San Marcos. Each commune will be treated as an individual cluster, and a random cluster sampling method will be employed to ensure a fair and unbiased selection of the communes for both the treatment and control groups.

The random selection will be carried out using a lottery system where each commune will be assigned a unique identifier, and a computerized random number generator will select the treatment commune and control communes. This approach minimizes selection bias and ensures a randomized, equitable process.

The 1:2 allocation ratio (one treatment commune and two control communes) was chosen due to feasibility considerations and community input. The local community expressed a preference for starting the Nutritional Forest intervention in one commune initially, allowing for more focused implementation and monitoring. This also aligns with the available resources and ensures that the intervention can be tailored to the specific needs of the treatment community.

Following the selection of the commune, we will proceed to sample households within each of the chosen commune. Household selection will be conducted using a two-stage sampling method. First, a list of households within each commune will be obtained from local community records. Second, a systematic sampling method will be applied to randomly select households from this list, ensuring that the sample is representative of the entire community. This step will ensure that our assessment captures a broad spectrum of community experiences and perspectives regarding the impact of the Nutritional Forest intervention.

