### 3.4 Sample size

A total of 968 families were considered as the research units in this study. Therefore, considering a margin of error of 5% and a confidence level of 95%, the estimated sample size before considering the finite population correction was approximately 384, according to Equation 1 where n is the sample size, Z is the Z-score associated (1.96) with the desired confidence level (95%), p is the estimated proportion of the attribute present in the population (0.5), and E is the margin of error (5%). After applying finite population correction, the estimated sample size was reduced to 276. This adjustment is made because the population is relatively small, and the correction helps avoid overestimating the required sample size. The sample of families in each commune is 300 because attrition is expected. The heads of the household will be surveyed regarding the nutritional, socioeconomic, and health situation of the family. The primary sampling unit for this study is the household (family unit), with a total sample size of 300 families. Within each family, specific questionnaires will be administered based on the nature of the assessment. The *Household Food Insecurity Access Scale (HFIAS)* will be completed by the head of the household to capture food security at the family level. For health and quality of life assessments, individual adult members will complete the *Short Form-36 Health Survey (SF-36)* and the *World Health Organization Quality of Life (WHOQOL-100)* questionnaire to evaluate personal health and quality of life outcomes. Additionally, the *Pediatric Quality of Life Inventory (PedsQL)* will be administered to caregivers of children to assess child health-related quality of life. This approach ensures comprehensive measurement across family and individual levels, providing both household-level insights and individual health metrics.

Formula for sample size estimation.

(1)
$$\begin{array}{l} n=\frac{Z^{2}\times p\times \left(1-p\right)}{E^{2}} \end{array}$$

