### 4.3 Potential pitfalls and unintended effects

Several potential pitfalls and unintended effects could arise during the implementation and evaluation of the Food Forest initiative. One key challenge is the variability in participant engagement. Some community members may be more actively involved in the initiative (e.g., planting, maintaining, or harvesting), while others may not fully engage, leading to differences in outcomes that may not directly reflect the intervention's effectiveness. Additionally, external factors, such as adverse weather conditions, could impact the growth of the Food Forest and, consequently, its effects on nutritional outcomes. Furthermore, there may be difficulties in retaining participants for follow-up assessments over the twelve-month study period, particularly given the rural nature of the setting, which may affect the continuity of data collection. To mitigate these risks, we will implement regular check-ins with participants, provide incentives to encourage continued engagement, and monitor environmental conditions closely to assess their impact on the project. By anticipating these challenges, we aim to minimize their potential effects on the study's results.

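### Section 3.10 names the pooled-variance Student's t-test while section 3.3 sets 1:2 allocation; its standard error is off if the spreads differ, and Welch's test removes that risk at almost no cost

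*Protocol article*

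**What the plan says.** **The test.** Section 3.10 compares continuous outcomes between arms (income change, BMI, dietary diversity scores) by Student's method: "t*-tests will be used if the data are normally distributed". Otherwise it switches to Mann-Whitney. The switch depends on normality alone; unequal spread is not considered. The same section plans linear regression and mixed-effects models for such outcomes and sets the level: "All hypothesis tests will be two-tailed, and a *p* < 0.05 will be considered statistically significant".

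**Group sizes.** Section 3.3 states and justifies unequal arms: "The 1:2 allocation ratio (one treatment commune and two control communes) was chosen due to feasibility considerations and community input". Section 3.4 adds "The sample of families in each commune is 300 because attrition is expected", which gives 300 treated and 600 control families.

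**What conflicts with this.** Section 3.1 describes a single control commune: "The study randomly allocated one commune to receive the Food Forest intervention, while a similarly characterized commune was randomly assigned as a control group". The Abstract says the same. Section 3.4 also speaks of a sample "with a total sample size of 300 families".

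**Uneven response.** Section 4.3 warns: "Some community members may be more actively involved in the initiative (e.g., planting, maintaining, or harvesting), while others may not fully engage". It cautions that results could then vary for reasons other than how well the food forest works. No SD or variance ratio for either arm appears anywhere.

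**The concern.** Student's t-test estimates one common variance from both arms. With equal group sizes, unequal variances do almost no harm. With a 1:2 split the larger arm dominates the pooled estimate. If the smaller, treated arm is the more variable, the pooled standard error is too small: a null difference is declared significant too often and confidence intervals are too narrow. If the control arm is the more variable, the test is conservative and loses power.

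There are two reasons not to assume equal spread. First, whole communes are drawn by lottery from the 18 listed in section 3.3, and one is treated. The treated arm's variance is that commune's variance, and nothing makes it equal to the variance across two other communes, even if the food forest changes nothing. Second, if some treated families respond and others do not, spread in the treated arm grows. Ordinary linear regression with conventional standard errors carries the same equal-variance assumption.

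**Working it through.** **Group size, reproduced from section 3.4.** With Z = 1.96, p = 0.5, E = 0.05 and N = 968:

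- n0 = 1.96² × 0.5 × 0.5 / 0.05² = 384 (stated: 384).
- With finite population correction: 384.1 / (1 + 383.1/968) = 275.2 (stated: 276).
- 276/300 = 0.92, so 300 per commune allows for 8% attrition.

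These are precision figures for one commune. They supply no SD.

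**Effect of pooling.** Inputs: n1 = 300 and n2 = 600 (sections 3.3 and 3.4), two-sided 5% level (section 3.10). Assumption: treated/control SD ratio r from 0.8 to 2.0, with control SD set to 1.

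- True variance of the mean difference: r²/n1 + 1/n2.
- Pooled variance: [((n1 − 1)r² + (n2 − 1)) / (n1 + n2 − 2)] × (1/n1 + 1/n2).
- k = √(pooled/true).
- Actual error rate = 2 × (1 − Φ(1.96k)).

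Worked at r = 1.5:

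- Pooled = [(299 × 2.25 + 599)/898] × 0.005 = 0.00708.
- True = 2.25/300 + 1/600 = 0.00917.
- k = √(0.00708/0.00917) = 0.879.
- Error rate = 2 × (1 − Φ(1.723)) = 8.5%.

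The last two columns are simulations of independent normal data with no mean difference, 40,000 trials per setting.

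| r | Pooled SE / true SE | Error rate, formula | Student, simulated | Welch, simulated |
|---|---|---|---|---|
| 0.8 | 1.076 | 3.5% | not run | not run |
| 1.0 | 1.000 | 5.0% | 5.1% | 5.1% |
| 1.1 | 0.969 | 5.8% | 5.6% | 4.9% |
| 1.2 | 0.942 | 6.5% | 6.5% | 5.0% |
| 1.5 | 0.879 | 8.5% | 8.7% | 5.1% |
| 2.0 | 0.816 | 11.0% | 11.0% | 4.9% |

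The ratio of group sizes drives this, not the total. At 100 v 200 (300 families in all) the formula gives 3.5% at r = 0.8 and 11.0% at r = 2.0.

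**At 1:1.** With n1 = n2 the pooled and true variances are algebraically the same. At 300 v 300, simulated error for r from 1.0 to 2.0 was 4.9% to 5.2% for both tests.

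**How large r might be from uneven response.** Assume a fraction f of treated families gain d control SDs and the rest are unchanged. Then r = √(1 + f(1 − f)d²).

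- f = 0.5, d = 0.5: r = √1.0625 = 1.03; SE 1.0% too small; tail probability 5.2%.
- f = 0.5, d = 1: r = √1.25 = 1.12; SE 3.6% too small; tail probability 5.9%.

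The mean effect is not zero in these two cases, so the figures are best read as non-coverage of a nominal 95% interval.

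**For scale: commune clustering.** Take 300 families per commune and an assumed ICC (the protocol gives none). The design effect is 1 + 299 × ICC, and with one commune per arm the naive/true variance ratio is (1 − ICC)/(design effect). At ICC 0.01 this is 0.99/3.99 = 0.248, and the error rate is 2 × (1 − Φ(1.96 × √0.248)) = 33%. At ICC 0.005, 0.02 and 0.05 it is about 22%, 46% and 63%. The results are almost the same at 1:2.

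**The case against.** The case against has real force.

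- **No variances are given.** At equal SDs the error rate is 5%, and at r below 1 the test is conservative, so neither the existence nor the direction of an error is established. This stands. A reader might infer that the 5% level is wrong as a matter of fact; the protocol does not support that.
- **Section 4.3 does not predict a larger treated variance.** It warns that uneven engagement complicates interpretation. A reader might take it as a forecast of wider spread in the smaller arm, but that is an inference. If the forest affects nobody, engagement adds no variance. If some gain and nobody loses, the mean effect is not zero and type I error is not the issue. Inflation by this route needs gains offset by losses, which nothing in the protocol suggests. This stands against the engagement argument. It does not touch the other argument, that different communes can differ in spread with no effect at all, nor the interval coverage when there is an effect.
- **300 v 600 is unsettled.** The Abstract and section 3.1 imply 1:1, where pooling is harmless. Section 3.10 also analyses nutritional status by individual, so family counts are not the sample for BMI. Both stand. The individual-level ratio is near 1:2 only if numbers per household are similar across arms.
- **Test variants are often left to an analysis plan.** This stands in part. The protocol does not specify the regressions' standard errors, so that part is a consequence of the point and not a separate fault. The t-test is different: section 3.10 names it and gives one condition for its use.
- **Clustering is the bigger problem.** Agreed. A sound commune-level analysis might replace the t-test altogether.

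**Conclusion.** The point holds as a minor, conditional one. The protocol names an equal-variance test beside an unequal allocation, and nothing in the design makes the spreads equal. Under 1:2 allocation and assumed SD ratios of 0.8 to 2.0, the nominal 5% becomes about 3.5% to 11%. Under moderate uneven response the standard error is only about 1% to 4% too small. Under 1:1 with equal numbers there is no error. These figures treat families as independent and normally distributed, and the SD ratios are assumptions, not protocol figures.

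A reader might also infer that changing the test would restore the stated error rate. It would not: tests on families or individuals that ignore the commune remain far from 5% at even small assumed ICCs, whichever t-test is used.

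**What to change.** In section 3.10, replace Student's t-test with Welch's unequal-variance t-test, and state that the linear regressions use variance-robust standard errors. Do not make the choice depend on a preliminary test of variances.

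The cost is about one sentence and a software option in Stata, which the protocol already names. If variances are equal the power loss is negligible, and at 1:1 the two tests behave alike, so the change is safe under either allocation.

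Two matters come first. Reconcile section 3.3 with the Abstract and section 3.1 on the number of control communes, and section 3.4 with itself on 300 families per commune or in total. Then settle how the analysis reflects allocation by commune. If that replaces the family-level t-test, this change applies only to whatever two-sample comparisons and regressions remain.

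### Ordered outcomes with three or more levels are assigned to multinomial logistic regression, which is valid but ignores the order and loses efficiency when the shift is in one direction

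*Protocol article*

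**What the plan says.** Section 3.10 of the protocol article gives one regression rule for all outcomes with more than two categories: "multinomial logistic regression will be used". It illustrates the rule with two outcomes:

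- an ordered one: "For outcomes with multiple categories, such as levels of health perception (good, fair, poor";
- one with no clear order: "employment status (employed, unemployed, seeking work".

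Section 3.9.2 defines the socioeconomic secondary outcome by placing each family's "socioeconomic level into one of five strata". Section 3.10 does not say how those strata will be modelled.

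For repeated measures, section 3.10 says that "mixed-effects models (both linear and logistic) will be employed". The error rate is set by "All hypothesis tests will be two-tailed" and a threshold of p < "0.05 will be considered statistically significant". Section 3.10 names no ordinal model.

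**The concern.** Good, fair and poor form a scale, and a family's socioeconomic level does too. A multinomial model treats the categories as unordered labels. For a two-group comparison it spends 2 degrees of freedom on three levels and 4 on five, and it reports two or four odds ratios. Its overall test says whether the groups differ, but not whether people moved up.

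The objectives are directional: the initiative is meant to improve health and household economic conditions. General health perception appears in the specific objectives (section 2.2) and in the secondary outcomes (section 3.9.2). Nothing else in section 3.10 uses the order of a categorical outcome. Group comparisons of categorical variables use chi-square or Fisher tests, and the rank test is reserved for continuous variables. At stake are efficiency and a clear effect measure for secondary outcomes.

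**Working it through.** **Inputs from the protocol article**
- Model for several categories: multinomial (3.10).
- Health perception: three levels (3.10), so 2 df for two groups.
- Socioeconomic level: five strata (3.9.2), so 4 df if the rule applies to it.
- Two-sided alpha 0.05 (3.10).
- 300 families per commune (3.4). Section 3.1 describes one control commune (300 v 300) and section 3.3 describes two (300 v 600).

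**Inputs assumed, because the article gives none:** ordinal power of 50% to 95%, odds ratios of 1.0 to 2.0, several category distributions, and independent observations.

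**Step 1. The plan's own figure.** Section 3.4 is a precision calculation: n0 = 1.96² × 0.5 × 0.5 / 0.05² = 3.8416 × 0.25 / 0.0025 = 384.16, stated as about 384. The finite population correction gives 384.16 / (1 + 383.16/968) = 275.2, which rounds up to the stated 276. The figures reproduce. No power or effect size enters, so the plan has no power target against which to judge either model.

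**Step 2. Ordinal against multinomial under proportional odds.** If one common odds ratio describes the shift, both tests have about the same noncentrality λ, but the ordinal test uses 1 df and the multinomial test K − 1. For 80% power on 1 df, λ = (1.960 + 0.842)² = 7.85. The same λ gives 70.9% power on 2 df and 59.5% on 4 df. Repeating this for other levels of ordinal power:

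| Ordinal power (1 df) | Multinomial, 3 levels (2 df) | Loss, points | Multinomial, 5 levels (4 df) | Loss, points |
|---|---|---|---|---|
| 50% | 40.1% | 9.9 | 30.8% | 19.2 |
| 60% | 49.5% | 10.5 | 38.9% | 21.1 |
| 70% | 59.7% | 10.3 | 48.2% | 21.8 |
| 80% | 70.9% | 9.1 | 59.5% | 20.5 |
| 90% | 83.5% | 6.5 | 74.0% | 16.0 |
| 95% | 90.8% | 4.2 | 83.7% | 11.3 |

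The largest possible loss is 10.5 points for three levels and 21.8 for five.

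**Step 3. Simulation check.** 20,000 runs per setting compared the multinomial likelihood-ratio test with the tie-corrected Wilcoxon test, which is the proportional-odds score test. At about 80% ordinal power, with 276 v 276 or 300 v 600, the loss was 8.7 to 9.6 points for three levels and 20.2 to 20.9 for five. It was much the same for each category mix and allocation. With no effect, the multinomial test rejected in 4.8% to 5.5% of runs, so its type I error is sound when observations are independent.

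**Step 4. When odds are not proportional** (three levels, 276 per group):

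| Control | Treatment | Multinomial power | Ordinal power |
|---|---|---|---|
| 30/50/20 | 35/40/25 | 55% | 5% |
| 30/50/20 | 30/60/10 | 89% | 35% |
| 30/50/20 | 20/60/20 | 73% | 45% |

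In these patterns the change is not a consistent shift along the scale, and the multinomial test does better.

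**The case against.** Multinomial regression is a legitimate model for ordered data. It makes no proportional-odds assumption, holds its type I error, and wins when the shift is uneven. The efficiency gain in Step 2 is computed in the setting that suits the ordinal model best, and the article supplies no effect size or category distribution to show that this setting applies. The same sentence of 3.10 also covers employment status, for which multinomial regression is suitable. All of this stands, and it limits the point to efficiency and clarity of reporting.

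Four stronger readings are tempting, and the article does not support them:

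- *A reader might infer a general loss of 10 to 20 points.* The only ordered outcome named in 3.10 has three levels, where the loss cannot exceed about 10.5 points. The 20-point figure needs five levels, and applying the rule to the strata is an inference from its general wording.
- *A reader might call these outcomes underpowered.* Section 3.4 sizes the study on precision, so there is no power target to miss.
- *A reader might conclude that ordered outcomes have no longitudinal model.* The word logistic in the mixed-effects sentence does not exclude multi-category forms, and an article may leave that detail to a fuller plan.
- *A reader might expect the category-wise odds ratios to contradict each other.* Nothing here shows that they would.

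What survives is that the article fixes, for an explicitly ordered outcome, a model that discards the order, while the scientific question has a direction.

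**Conclusion.** The point holds as a low-severity improvement. The stated model is valid but inefficient and indirect for ordered outcomes. Under proportional odds and independent observations, at 80% ordinal power, it gives up about 9 points of power for three levels and about 20 for five. For the named three-level outcome, the loss runs from about 4 to 10.5 points over ordinal power of 50% to 95%. The five-level figure applies only if the general rule is meant to cover the socioeconomic strata.

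The figures are a relative comparison only. With one treatment commune and one or two control communes, and several members per family for individual-level outcomes, absolute power is lower than shown under either model. That is a separate and larger matter, which changing the model for ordered outcomes does not solve. If the effect is not a consistent shift, the ranking of the two models can reverse. The case for one directional effect measure does not depend on the power figures, though a single odds ratio summarises the effect well only where proportional odds is reasonable.

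**What to change.** Amend the sentence in section 3.10 as follows:

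1. For ordered outcomes (health perception and, if analysed as categories, the five socioeconomic strata), use ordinal (proportional-odds) logistic regression and report one odds ratio with its 95% CI. State explicitly how the strata will be analysed.
2. For the longitudinal analysis of these outcomes, use mixed-effects ordinal logistic regression. Either treat baseline as one of the repeated outcomes, with a group-by-time term, or enter baseline category as a covariate and model only the follow-up visits. Do not do both. Section 3.10 currently lists baseline among the repeated measures, so the second option means changing that list for these outcomes.
3. Check proportional odds, and name a partial proportional-odds or multinomial fit as the sensitivity analysis.
4. Keep multinomial regression for nominal outcomes such as employment status.

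The cost is a few lines of text and a different model command, with no new data and no design change. The downside is reliance on the proportional-odds assumption, which item 3 addresses.
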